### Sample Size Calculation

An a priori power analysis was conducted using G*Power. On the basis of meta-analyses of related VR-based mental health interventions [30,31], a medium effect size (f=0.25) was assumed. To achieve 80% power at an alpha level of .05 for the primary group-by-time comparison, a required sample of 90 participants was indicated. To account for an anticipated attrition rate of 20% to 30%, consistent with rates reported in VR intervention literature, the recruitment target is set at 110 participants. A sensitivity analysis indicates that with 30% attrition (leaving approximately 77 participants), statistical power for the primary comparison would be reduced to approximately 70%, which is acknowledged as a limitation. To minimize attrition, the study will implement flexible scheduling, session reminders, brief mid-study check-ins, and graduated VR exposure in the first session to identify and manage cybersickness early. If observed attrition exceeds 30%, this will be reported transparently and considered in the interpretation of results. This sample size determination was made for the primary clinical outcomes and was not specifically powered for mediation or moderation analyses; those analyses will therefore be treated as exploratory.

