### Outcomes

#### Primary Outcomes

The primary outcome will be the change in symptom severity for depression and anxiety.

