##### Music-Movement Synchronization

Music-movement synchronization is an objective behavioral metric captured by the VR software, reflecting the accuracy and timing of participants’ physical movements relative to musical beats. Within the SDT framework, this variable is treated as an exploratory behavioral indicator that may reflect task engagement and perceived competence. It is not a primary or confirmatory outcome; any associations with other variables will be interpreted as hypothesis generating.

All self-report and fitness measures will be collected at T0, T1, and T2. In-VR behavioral data will be captured continuously during the intervention period.

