### Data Management

All data will be entered into a secure electronic database with verification procedures. Identifiable information will be stored separately from outcome data on encrypted institutional servers, accessible only to authorized members of the research team.

For the primary outcomes, linear mixed-effects models will be used to examine group, time, and group×time effects on BDI-II and BAI scores. Separate models will be fitted for depression and anxiety outcomes, with participant-level random intercepts to account for repeated measures over time. Gender and primary presenting concern (the stratification variables) will be included as covariates, and baseline symptom severity will be considered in model specification as appropriate. The primary planned contrasts will compare the experimental group with the active control group at T1 and T2; comparisons involving the waitlist control group will be secondary and should be interpreted with caution, given the expectancy and novelty confounds inherent in waitlist comparisons. Post hoc pairwise comparisons will be adjusted for multiple testing using a Holm procedure. Secondary outcomes will be analyzed using analogous mixed-model approaches. Cybersickness (SSQ scores) will be examined as a potential covariate in sensitivity analyses to assess whether differential simulator sickness across groups confounds the primary results. Missing data assumptions will be examined, with maximum likelihood estimation in mixed models as the primary approach and multiple imputation and per-protocol analyses used as sensitivity analyses where appropriate. Exploratory analyses will examine whether changes in Basic Psychological Need Satisfaction Scale scores are associated with changes in BDI-II and BAI scores and whether music-movement synchronization moderates selected outcomes; these analyses will be interpreted as hypothesis generating rather than confirmatory causal tests.

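### The primary mixed model leaves its baseline term open and does not say whether the T1/T2 contrast is a level or a change; the wording permits both inefficient and anti-conservative models

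*Protocol article*

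**What the plan says.** The analysis text stands under Data Management in the protocol article. It states that "linear mixed-effects models will be used to examine group, time, and group×time effects on BDI-II and BAI scores", in separate models for the two scales, "with participant-level random intercepts to account for repeated measures over time". Gender and presenting concern are named as covariates. Baseline is treated differently: "baseline symptom severity will be considered in model specification as appropriate". On the test itself: "The primary planned contrasts will compare the experimental group with the active control group at T1 and T2".

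Three other places bear on how T0 enters the model:

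- Primary Outcomes: "The primary outcome will be the change in symptom severity for depression and anxiety".
- Sample Size Calculation: "To achieve 80% power at an alpha level of .05 for the primary group-by-time comparison, a required sample of 90 participants was indicated".
- Music-Movement Synchronization (closing paragraph): "All self-report and fitness measures will be collected at T0, T1, and T2".

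No section says outright whether T0 is one of the modelled outcomes, whether baseline will be a covariate beside it, or whether the contrast at T1 and T2 is a difference in level or in change from T0.

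**The concern.** The article commits to a covariance structure and to two covariates, but leaves the most influential remaining term of the primary model to discretion. A change outcome, a power statement about group by time, and three repeated measures all make T0 as an outcome the natural reading. On that reading the open clause leads to two unsatisfactory places.

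- If baseline is not a covariate, the contrast uses the measured baseline poorly or not at all. The sample size section already concedes about 70% power at 30% attrition.
- If baseline is added as a covariate, the same number sits on both sides of the equation. The T0 residuals become very small, and the random-intercept model assumes one variance for all times. The small T0 residuals therefore pull down the standard error at T1 and T2, and the primary test rejects too often.

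The choice changes the p value. Randomization and Blinding says analysts work on coded groups until the primary models are final. Coding is only partial protection, because the two-sided p value for two arms is the same whichever code belongs to which arm.

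**Working it through.** **Inputs.** From the document: the model terms, the random intercept, three times, 110 participants allocated 1:1:1 (simulated as 37/37/36), and 20% to 30% expected attrition. Assumed, because the document gives neither: equal variance at each time (set to 1) and a common correlation ρ between times (compound symmetry). The plan states no standard error, so there is no figure of its own to reproduce on this point.

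**1. T0 as outcome, baseline not a covariate.** Per-person contrast variance is 1 for a level and 2(1−ρ) for a change. With baseline adjustment it is 1−ρ². The variance penalties are therefore 1/(1−ρ²) and 2/(1+ρ):

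| ρ | level | change |
|---|---|---|
| 0.3 | 1.10 | 1.54 |
| 0.5 | 1.33 | 1.33 |
| 0.7 | 1.96 | 1.18 |

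**2. T0 as outcome and baseline also a covariate, level contrast.** The fitted slope is the regression of a person's three-visit mean on T0: b = (1+2ρ)/3. The true residual variance is (1−b)² at T0 and 1−2bρ+b² at T1 and T2. The model applies the average of the three to every time. Dividing that average by the T1 value gives

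model variance / true variance = (4+2ρ)/(5+4ρ).

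At ρ = 0.5, b = 0.667. The residual variances are 0.111, 0.778 and 0.778, with average 0.556. The ratio is 0.556/0.778 = 5/7, and √(5/7) = 0.845, so the standard error is 15.5% too small. Over the range:

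| ρ | 0.25 | 0.3 | 0.4 | 0.5 | 0.6 | 0.7 | 0.8 |
|---|---|---|---|---|---|---|---|
| SE too small by | 13.4% | 13.9% | 14.7% | 15.5% | 16.2% | 16.8% | 17.4% |

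**3. Simulation check.** REML random-intercept fits, 3,000 trials per row, no true effect, two-sided 5% test at T1. Dropout is at random, before T1 or before T2. Gender and presenting concern are omitted. SE ratio is mean model SE over the actual SD of the estimate.

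| ρ, dropout | T0 in both roles, level: SE ratio, type I | T0 in both roles, change: SE ratio, type I | T1/T2 outcomes with baseline covariate: SE ratio, type I |
|---|---|---|---|
| 0.3, 0% | 0.856, 9.2% | 0.985, 5.5% | 0.999, 4.7% |
| 0.5, 0% | 0.838, 9.7% | 0.989, 5.4% | 0.995, 4.8% |
| 0.7, 0% | 0.835, 10.0% | 1.009, 5.1% | 1.000, 4.9% |
| 0.5, 25% | 0.810, 11.2% | 0.955, 6.6% | 1.002, 4.5% |
| 0.5, 30% | 0.800, 11.8% | 0.942, 6.8% | 1.000, 4.8% |

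Dropout worsens the level contrast because T0 rows become a larger share of the data. With T0 as outcome and no baseline covariate, the SE ratio was 0.99 to 1.01 for both contrasts, so step 1 concerns efficiency and not validity.

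**4. Other correlation patterns.** The same calculation with unequal correlations (T0–T1, T0–T2, T1–T2) moves the figure. With 0.6, 0.36, 0.6: b = 0.653; residual variances are 0.120, 0.643 and 0.956, average 0.573. SE ratios are √(0.573/0.643) = 0.944 at T1 and √(0.573/0.956) = 0.774 at T2, that is 6% and 23% too small. With 0.4, 0.3, 0.6 the shortfalls are 12% and 17%. Across the patterns tried the range was 6% to 23%.

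The random intercept can also misstate a change contrast. With 0.5, 0.5, 0.8 the fitted within-person variance is (0.5+0.5+0.2)/3 = 0.4 against a true 0.5 for T1 minus T0. The ratio is √(0.4/0.5) = 0.894.

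**The case against.** The strongest reply is that the document never commits to the faulty model. Time and group-by-time terms also exist when only T1 and T2 are outcomes, and the contrasts are placed at those two times. The wording therefore also admits a valid and efficient model with baseline as covariate, or one with a constrained baseline. A reader might infer that the plan must either waste the baseline or inflate type I error. That does not follow, because those two outcomes are not exhaustive.

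The change definition of the outcome and the group-by-time power statement also point towards a change contrast. For that contrast the double use of T0 does little harm: under compound symmetry the SE is about right without dropout, and 5% to 6% too small with 25% to 30% dropout. This stands, and the level-contrast figures must be labelled as such. It does not remove the point, since the text leaves level or change open and a change contrast is still less efficient than baseline adjustment.

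A reader might also take one percentage as a property of this trial. No correlation or SD is given, so only a conditional range is supportable. It is also tempting to argue that the eligibility cut-offs compress the T0 spread and shrink the standard error further. The inclusion criteria accept a qualifying score on BDI-II or on BAI, so neither scale is confined to its own window in everyone, and the document gives no basis for any particular SD ratio. That argument is not used here.

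Finally, a statistical analysis plan that is not shown may settle the model. If so, the published sentence still needs to agree with it. Degrees-of-freedom methods can properly be left there.

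**Conclusion.** The point holds as a weakness of specification. It is not a demonstrated error in a committed analysis. The baseline term of the primary model is discretionary, and the T1/T2 contrast is undefined as level or change.

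The size depends on T0 being an outcome, which is natural but unstated. Leaving baseline out then costs a variance factor of 1.10 to 1.96 (level) or 1.54 to 1.18 (change) for ρ of 0.3 to 0.7. Using T0 in both roles makes the level-contrast SE about 13% to 17% too small under compound symmetry, and about 20% too small with 25% to 30% dropout. Type I error is then about 9% to 10% and 11% to 12% respectively. Every figure rests on assumed correlations. The direction of the double-use error for a level contrast was the same in every pattern tried. The plan should be changed, since the remedy is free and rules out an anti-conservative model that the present wording permits.

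**What to change.** Replace the open clause on baseline severity with one fixed primary model, chosen from:

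- T1 and T2 as outcomes; fixed effects for group, time, group by time, baseline score of the same scale, baseline by time, gender and presenting concern; or
- a constrained longitudinal model with T0, T1 and T2 as outcomes and a common T0 mean across arms. This also keeps participants who have T0 only.

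State that T0 will not be both outcome and covariate under a random intercept. Replace the random intercept by an unstructured within-person covariance. Define the primary contrast as the baseline-adjusted difference between experimental and active control groups at T1 and at T2. With the baseline score as covariate, a difference in level and a difference in change are the same quantity, so this also settles that ambiguity.

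The cost is a few sentences. Baseline is already collected, no extra data are needed, and the Results section reports that no participant had been enrolled as of April 2026. Under the compound-symmetry assumptions above, the first option held type I error at 4.5% to 4.9% and recovers the precision lost by leaving baseline out.

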### Participant Timeline

Following screening and informed consent, eligible participants will complete baseline assessment (T0), undergo randomization, receive the 6-week intervention or waitlist condition, complete the postintervention assessment at week 6 (T1), and complete the follow-up assessment at week 10 (T2; Table 1).

**Table 1 table1:** Schedule of enrollment, interventions, and assessments.

Time point	Enrollment	Allocation	T0^a^	T1^b^	T2^c^
Eligibility screen	✓				
Informed consent	✓				
Randomization		✓			
Intervention			✓		

^a^T0=baseline: week 0.

^b^T1=posttest: week 6.

^c^T2=follow-up: week 10.

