### Interventions

#### Experimental Group: VR Social Musical Exergame

Participants in this arm will engage in the VR intervention twice a week for 45 minutes over 6 weeks. Prior to the first intervention session, all participants in VR conditions (experimental group and active control group) will complete a 15-minute familiarization session using a neutral, nontherapeutic VR environment to reduce initial novelty effects and identify individuals who may experience significant cybersickness. Waitlist control participants will receive a brief (5-minute) VR demonstration to partially equalize technology exposure. The experimental condition is conceptualized as a bundled social VR musical exergame designed to support autonomy, competence, and relatedness simultaneously.

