#### Waitlist Control Group

Participants in this group will receive a standardized digital handbook on mental health. They will be instructed to maintain their usual activities for the 6-week study period. To address ethical considerations, this group will be offered access to the VR intervention after the trial. Comparisons with this group are intended as secondary estimates of effects relative to minimal guidance rather than as the primary test of the social mechanism.

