### Safety Monitoring and Adverse Events

Adverse events will be monitored throughout the trial. Participants will be asked about dizziness, nausea, eyestrain, disorientation, social distress, and symptom worsening at each VR session and at formal assessment points. The Simulator Sickness Questionnaire (SSQ) will be administered at the end of every VR session to track habituation trajectories and detect differential cybersickness across groups; SSQ scores will be examined as a potential covariate in sensitivity analyses. Sessions may be paused or discontinued if participants experience clinically meaningful discomfort. All adverse events and withdrawals will be recorded.

Predefined clinical thresholds will be used to identify participants requiring immediate attention. A BDI-II total score exceeding 28 (indicating severe depression) or any endorsement of suicidal ideation on BDI-II item 9 (score ≥1) at any assessment point will trigger immediate clinical review. Similarly, a BAI total score exceeding 25 (indicating severe anxiety) will prompt review. Self-report assessments will be scored in real time at each formal assessment point, with automatic flagging of scores exceeding these thresholds. Session facilitators will also conduct a brief verbal check-in before and after each VR session to monitor participant well-being.

When a clinical threshold is met, the session facilitator will immediately notify the principal investigator, who will conduct or arrange a clinical risk assessment within 24 hours. Participants meeting clinical concern criteria will be referred to the psychological counseling center at Hunan Traditional Chinese Medical College for nonurgent concerns or to the psychiatric emergency department at the nearest affiliated hospital for acute crises. The principal investigator ([name]) will serve as the designated safety officer responsible for overseeing all safety monitoring procedures and referral decisions. Participants who are referred for clinical care may continue in the trial if deemed safe by the assessing clinician or may be withdrawn if continued participation poses a risk to their well-being.

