The protocol also has important limitations that should be considered when interpreting future results. First, the 1-month follow-up captures only short-term stability rather than long-term remission; it cannot assess relapse patterns, sustained behavioral change, or long-term clinical trajectories, and future trials should include follow-up periods of at least 3 to 6 months. Second, the social condition is a bundled manipulation that combines voice chat, collaboration, competition, and visible performance comparison; therefore, the trial cannot isolate the independent effect of each social feature, and the study should be understood as a preliminary multicomponent efficacy trial that may inform future dismantling or factorial designs to identify active therapeutic ingredients. Third, the primary outcomes (BDI-II and BAI) are self-report measures administered in an unblinded trial, which increases susceptibility to expectancy, demand characteristics, and placebo effects, particularly given the immersive and novel nature of the VR intervention; future trials should consider incorporating clinician-administered measures (eg, the Hamilton Depression Rating Scale) or objective biomarkers alongside self-report instruments. Fourth, although the intervention is informed by SDT, the bundled design does not isolate or manipulate autonomy, competence, and relatedness independently; any associations between need satisfaction and symptom change are therefore exploratory and cannot establish causal mediation. Fifth, differential cybersickness between the social and solo VR conditions could confound group comparisons, as more complex social interactions may elicit different levels of simulator sickness. Sixth, the study is powered for the primary clinical outcomes but not specifically for mediation or moderation analyses, which are therefore exploratory and hypothesis generating. Finally, although the eligibility range has been narrowed to 18 to 25 years to reduce developmental heterogeneity, individual differences within this developmental period may still influence intervention response.

If the intervention demonstrates favorable short-term effects and acceptable safety, the findings may support a scalable and engaging digital mental health approach that is feasible on consumer-grade VR hardware. The protocol may also inform future dismantling studies that test specific social features, as well as trials with longer follow-up and broader multisite implementation.

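### SSQ is recorded after randomisation and may be changed by the social condition, so adjusting for it cannot test whether the primary comparison is confounded

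*Protocol article*

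**What the plan says.** The analysis text, under Data Management in the protocol article, states: "Cybersickness (SSQ scores) will be examined as a potential covariate in sensitivity analyses". The purpose given is "to assess whether differential simulator sickness across groups confounds the primary results". Safety Monitoring and Adverse Events announces the same covariate use and sets the timing: "The Simulator Sickness Questionnaire (SSQ) will be administered at the end of every VR session".

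The fifth limitation in the Discussion uses the same reasoning: "differential cybersickness between the social and solo VR conditions could confound group comparisons, as more complex social interactions may elicit different levels of simulator sickness".

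The order of events is in Participant Timeline: "eligible participants will complete baseline assessment (T0), undergo randomization, receive the 6-week intervention or waitlist condition". The waitlist arm has no intervention sessions during the study period. Its content is given as "Participants in this group will receive a standardized digital handbook on mental health", and its only VR exposure is described as follows: "Waitlist control participants will receive a brief (5-minute) VR demonstration to partially equalize technology exposure". No SSQ is mentioned for that demonstration.

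The primary models for BDI-II and BAI adjust for the two stratification factors, with baseline severity to be considered. SSQ is not among the primary covariates. The main contrast is the social arm against the solo arm at T1 and T2.

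**The concern.** A confounder of a treatment comparison is a common cause of treatment and outcome. Randomisation removes such causes in expectation, and nothing measured afterwards can be a cause of allocation. Session SSQ is measured afterwards, and the protocol itself supposes that the allocated condition may change it. It can therefore be a mediator (arm changes sickness, sickness changes mood) or a collider (arm and some personal trait both change sickness, and the trait also changes mood). It cannot be a confounder of social versus solo play.

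The trial asks what the bundle of social features adds to solo play. Sickness that those features provoke or relieve belongs to that answer.

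What is at stake is interpretation. The SSQ-adjusted result is offered as a validity check on the primary result. If the two differ, a reader following the stated purpose would conclude that the randomised result is confounded. If they agree, the reader would take reassurance that the analysis cannot give.

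**Working it through.** The plan gives no SSQ figure to reproduce. The check has three steps: the order of events, the algebra of the adjustment, and the availability of SSQ by arm.

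**1. Order of events (from the protocol article).** Baseline, then randomisation, then the 6-week intervention with SSQ after each session, then T1 and T2. SSQ therefore lies between allocation and outcome. The Discussion supplies the possible arrow from social condition to SSQ.

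**2. What adjustment does.** A simple linear model of the social versus solo contrast, with G = 1 for social and 0 for solo:

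- SSQ = a·G + g·U + error, with within-arm variance 1
- Outcome = τ·G + b·SSQ + c·U + error

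U is an unmeasured trait that affects both SSQ and symptoms. Randomisation makes U independent of G, so there is no confounding in any scenario.

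- Unadjusted (total) effect: τ + a·b
- Given G and SSQ, the expected U is g·(SSQ − a·G), so the SSQ-adjusted group coefficient is τ − a·c·g
- Adjusted minus total: −a·(b + c·g)

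The document has no SSQ data, so all inputs are assumptions: τ = −0.5 (negative means benefit); a = −0.5, 0 or +0.5; b = 0 or 0.3; c = g = 0 or 0.4. Units are about one within-arm SD of the outcome. The SD is 1, or √(1 + 2·0.3·0.4·0.4) = √1.096 ≈ 1.05 when b and c are both nonzero. Values in brackets come from a simulation of 400,000 participants per scenario.

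| SSQ shift a | b | c = g | Total effect | SSQ-adjusted | Adjusted / total |
|---|---|---|---|---|---|
| +0.5 | 0.3 | 0 | −0.35 (−0.348) | −0.50 (−0.499) | 1.43 |
| +0.5 | 0.3 | 0.4 | −0.35 (−0.349) | −0.58 (−0.580) | 1.66 |
| +0.5 | 0 | 0.4 | −0.50 (−0.499) | −0.58 (−0.578) | 1.16 |
| −0.5 | 0.3 | 0 | −0.65 (−0.654) | −0.50 (−0.507) | 0.77 |
| −0.5 | 0.3 | 0.4 | −0.65 (−0.648) | −0.42 (−0.419) | 0.65 |
| −0.5 | 0 | 0.4 | −0.50 (−0.505) | −0.42 (−0.426) | 0.84 |
| ±0.5 | 0 | 0 | −0.50 | −0.50 | 1.00 |
| 0 | any of the above | any of the above | −0.50 | −0.50 | 1.00 |

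Worked example, second row: total = −0.5 + 0.5·0.3 = −0.35; adjusted = −0.5 − 0.5·0.4·0.4 = −0.58; difference = −0.5·(0.3 + 0.16) = −0.23.

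If social play raises sickness and sickness worsens mood (first two rows), adjustment removes a harm that the social condition causes and overstates its benefit. If social play lowers sickness, adjustment understates the benefit. In the third and sixth rows SSQ has no effect on symptoms, yet the shared cause alone moves the contrast by 0.5·0.16 = 0.08. In the last two rows adjustment changes nothing.

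**3. Availability by arm.** With 110 randomised 1:1:1, each arm has 110/3 ≈ 37 participants, and the two VR arms together about 73. At 30% attrition (77 left) the two VR arms have 77·2/3 ≈ 51. The waitlist arm has no scheduled session SSQ, so waitlist contrasts cannot be adjusted for it unless values are invented. The social versus solo contrast keeps both arms.

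**The case against.** The best reply is that this is a potential covariate in a sensitivity analysis and nothing more. The primary models do not use SSQ, and no rule lets an adjusted result override them. All of that stands, and it limits the weight of the point. It does not rescue the stated purpose, because the analysis cannot answer the question set for it. This is a wrong statement in the document, not a detail left to an analysis plan.

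A second reply is that much of the remedy is already present: SSQ is collected under safety monitoring to detect differences between groups, and withdrawals are recorded. That also stands, and it makes the fix cheap.

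A third is that the waitlist gap does not matter, since the check concerns the primary results and the Discussion locates the worry between the two VR arms. That largely stands. The gap affects only secondary contrasts, and the document does not say that SSQ would enter a three-arm model. How session scores are summarised and missed sessions handled can properly be left to the analysis plan.

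A reader might also infer more than the documents support:

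- That adjustment shrinks the effect. The direction depends on the sign of the SSQ difference, which the Discussion does not state.
- That bias is certain. The Discussion says only that sickness levels may differ. If they do not differ by arm, the adjusted and unadjusted contrasts agree.
- That a third of the sample is lost from the primary comparison. Both of its arms have SSQ.
- That the primary analysis is compromised. It is not.

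**Conclusion.** The point holds as a fault in the stated purpose and interpretation of one sensitivity analysis, and in the matching limitation. Session SSQ follows randomisation and may be affected by allocation, so it cannot confound the randomised social versus solo comparison. An SSQ-adjusted contrast is not the intention-to-treat effect and cannot diagnose confounding of it.

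Its size cannot be derived from the documents. In the illustrative model the adjusted contrast ranges from 0.65 to 1.66 times the total effect, with 1.00 when SSQ does not differ by arm or is unrelated to outcome. These figures rest on assumed values and a linear model without an arm-by-SSQ interaction. They show that the discrepancy can go either way with no confounding present; they do not predict this trial.

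The conclusion on timing and causal role needs none of those assumptions. It rests on the protocol's own schedule and on its own statement that the social condition may change sickness.

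**What to change.** - In Safety Monitoring and Adverse Events and in Data Management, remove SSQ adjustment as a sensitivity check on the primary outcomes.
- Report SSQ, and withdrawals attributed to cybersickness, by VR arm as tolerability outcomes.
- If the part SSQ plays in the effect is of interest, specify an exploratory mediation analysis restricted to the two VR arms, with its assumptions stated (in particular, no unmeasured common causes of SSQ and symptoms). The protocol already treats its need-satisfaction analyses as exploratory and non-causal, and the same label fits here.
- Reword the fifth limitation so that differential cybersickness is described as part of the effect of the social condition, not as confounding.

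The cost is wording and the relabelling of one analysis. No added data, visits or participants are needed, and the protocol reports that nobody had been enrolled as of April 2026.

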### Data Collection and Analysis

Data collection will be conducted via a secure online survey platform and directly from the VR software. All primary analyses will follow the intention-to-treat principle and will include all randomized participants with available data.

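### Agreement between the mixed model, multiple imputation and the per-protocol analysis, as the protocol names them, cannot show whether not-at-random dropout would change the social-versus-solo result

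*Protocol article*

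**What the plan says.** The analysis text of the protocol article stands under Data Management. It promises that "Missing data assumptions will be examined", "with maximum likelihood estimation in mixed models as the primary approach". The sensitivity analyses it names for this are "multiple imputation and per-protocol analyses used as sensitivity analyses where appropriate". It gives no imputation model, no imputation assumption and no analysis that departs from missing at random (MAR).

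One further sensitivity analysis is listed: "Cybersickness (SSQ scores) will be examined as a potential covariate in sensitivity analyses". Its stated purpose is to check confounding by simulator sickness, not missing data.

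Under Data Collection and Analysis, the primary analyses "will include all randomized participants with available data". Sample Size Calculation plans for an "anticipated attrition rate of 20% to 30" percent. If attrition goes above that, the section promises transparent reporting and consideration in interpretation, but no analysis.

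Two other places bear on why people might leave. Safety Monitoring and Adverse Events says that participants referred for clinical care "may be withdrawn if continued participation poses a risk to their well-being". The Discussion lists cybersickness that differs between social and solo VR as a possible confounder.

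**The concern.** A sensitivity analysis for missing data is useful when it varies the assumption that the primary analysis cannot check. Neither named analysis clearly does so.

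- **Multiple imputation.** Named without a departure, it ordinarily assumes MAR, as the likelihood mixed model does. With the same variables it aims at nearly the same estimate.
- **Per-protocol.** It conditions on adherence after randomization. It answers a different question in a selected group and leaves the missingness assumption untouched.
- **Examining assumptions.** Observed data cannot separate MAR from not-at-random dropout, so the general promise to examine assumptions does not fill the gap.

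BDI-II and BAI are collected only at T0, T1 and T2. Someone who worsens and is lost before week 6 contributes only a baseline score to the primary model. What was noted at the VR sessions about discomfort, social distress or worsening is not in that model. With about 37 people per arm (110/3), 20% to 30% attrition is about 7 to 11 people per arm (36.7 × 0.2 = 7.3; 36.7 × 0.3 = 11.0). The primary contrast could move by a relevant fraction of its assumed size while all the planned analyses agree.

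**Working it through.** **1. The plan's own figure.** Retained participants = 110 × (1 − attrition). At 30%: 110 × 0.70 = 77, which matches the protocol. At 20%: 110 × 0.80 = 88.

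**2. Size of the bias.** Let p be the dropout share in an arm and δ the amount by which its dropouts are worse than MAR predicts from their observed data. Then

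bias in favor of the social arm ≈ p(social) × δ(social) − p(solo) × δ(solo).

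The attrition range is from the protocol. The values of δ are assumptions.

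- δ only in the social arm: 0.2 × 2 = 0.4 points, up to 0.3 × 5 = 1.5 points on the BDI-II.
- Equal p and equal δ in both arms: 0.
- δ only in the solo arm: the same size with the opposite sign.
- 30% dropout in social, 20% in solo, δ = 0.5 SD in both: 0.15 − 0.10 = 0.05 SD.

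**3. Relative to the assumed effect.** The protocol assumes f = 0.25. Read as a two-group effect, d = 2 × 0.25 = 0.5. The protocol gives no SD. With an assumed SD of 8 to 10 points, d = 0.5 is 4 to 5 points. The bias is then 0.4/5 = 8% to 1.5/4 = 37.5% of the effect. In SD units, with a one-arm δ at 20% to 30% dropout:

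| δ (SD) | Bias (SD) | Share of d = 0.5 |
|---|---|---|
| 0.25 | 0.05 to 0.075 | 10% to 15% |
| 0.5 | 0.10 to 0.15 | 20% to 30% |
| 1.0 | 0.20 to 0.30 | 40% to 60% |

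**4. Would the planned analyses reveal it?** Large-sample simulation: 6 runs of N = 6000, two arms, three time points, random intercept with correlation 0.5, true difference −0.50 SD, about 30% dropout per arm, dropouts missing at T1 and T2. Completers stand in for per-protocol. In the third row, dropout in the social arm depends on the unseen T1 score (log-odds 1 per SD) and is random in the solo arm. Monte Carlo error is about 0.02 SD.

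| Dropout | Mixed model | MAR imputation | Completers |
|---|---|---|---|
| Completely at random | −0.52 | −0.51 | −0.51 |
| At random given baseline | −0.52 | −0.51 | −0.51 |
| Not at random, social arm only | −0.68 | −0.69 | −0.68 |

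The three analyses agree in every row, including the one where all are wrong. In that third setting, delta-adjusted imputation in the social arm gives −0.54 at δ = 0.5 SD and −0.44 at δ = 0.8 SD. This follows the formula: −0.687 + 0.307 × 0.5 = −0.53 and −0.687 + 0.307 × 0.8 = −0.44. The delta analysis does not reveal the true δ. It shows how the answer depends on it.

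**5. Effect on interval coverage at the trial's size.** With 37 per arm, an assumed residual SD of about 7.7 and 3000 runs per setting:

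| Dropout, δ in social arm | Bias (points) | 95% interval coverage |
|---|---|---|
| 20%, 2 points | −0.43 | 94.5% |
| 30%, 3 points | −0.91 | 93.4% |
| 30%, 5 points | −1.45 | 89.8% |

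Coverage hardly moves except in the last setting, because the intervals are wide at this sample size. The estimate shifts more clearly than the coverage does.

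**The case against.** The strongest objection is that the protocol never says its imputation assumes MAR. This is a condensed article, and an analysis plan that is not shown could specify delta adjustment or auxiliary variables. That stands as a limit: MAR is the ordinary reading of imputation named without a departure, not something the document states. The point survives because the article does name its sensitivity analyses, and as named they leave the key assumption fixed.

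Three stronger readings are tempting and are not supported.

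- **That the protocol describes informative dropout.** It does not. For discomfort it speaks of pausing or discontinuing sessions, not of leaving the trial. It raises differential cybersickness as a confounder, without mentioning dropout. A withdrawal that follows a high recorded T1 score depends on observed data, which the mixed model can handle under MAR. These are possible routes to informative dropout, and they may differ by arm. They are no more than that.
- **That the bias favors the social arm.** This follows only if social-arm dropouts do worse, relative to prediction, than solo-arm dropouts. The arms share frequency, duration, intensity, content and music, so near-equal dropout and δ are plausible, and the bias would then largely cancel. It could also reverse.
- **That the planned analyses say nothing about attrition.** Imputation that adds measured variables such as SSQ scores can show whether dropout explained by those variables matters. The gap concerns dropout that is not at random.

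It is also fair that the sentence combines several items, so per-protocol may not be meant as a test of missingness. Its placement beside imputation still invites that reading.

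**Conclusion.** The point holds in limited form. Unless the imputation is specified to depart from MAR, agreement among the primary model, multiple imputation and per-protocol cannot show whether not-at-random dropout would change the social-versus-solo conclusion. For a one-arm δ of 2 to 5 BDI-II points, the possible shift at the expected attrition is 0.4 to 1.5 points, about 8% to 38% of a 4 to 5 point effect. The δ, the SD of 8 to 10, the reading of f = 0.25 as d = 0.5 and the confinement to one arm are assumptions. The documents settle neither the size nor the direction of any actual bias. This is an inexpensive improvement that should be made. It does not show that the primary analysis is invalid.

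**What to change.** - Supplement the imputation analysis with delta-adjusted multiple imputation for social versus solo, on BDI-II and BAI, at T1 and T2. Vary δ separately in each arm and report the tipping point, that is, the combinations at which the conclusion changes.
- State the assumption behind the base imputation. Use the SSQ scores, already planned after every VR session, and the recorded withdrawals as auxiliary information.
- Keep the per-protocol analysis, but label it supplementary rather than a missing-data sensitivity analysis.

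The cost is revised analysis wording, a little more programming and some extra reporting. No new data are needed. As of April 2026 the protocol reports that no participants had been enrolled, so the range of δ can be fixed before any outcome is seen.
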